### Blinding

The patient management team, including the consultant cardiologist, medical officers, and nursing staff, will be blinded to the nature of the intervention to which the patient is assigned. All the interview-based questionnaires will be administered to the patients by a research assistant, who will make sure the patients of either group are blinded to the intervention or other group during questioning. During the clinic follow-up visits, the participants will be advised not to convey information regarding the nature of the intervention they are undergoing to other study participants or to the attending clinician to avoid cross-contamination or breach of the single-blind study design, respectively. Furthermore, the participants within the control and intervention groups will be followed on different working days to ensure the quality of the study.

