As part of this 12-week hospital- and home-based intervention, each participant in the intervention group will be provided with a model plate along with the food poster and a food diary. The patients will also be provided with nutrition advice that will be customized according to patients’ social, economic, and personal preferences by a trained research assistant (PF) with close supervision of a nutrition specialist (RJ). Advice in other domains, such as physical activity and lifestyle modification (e.g., cessation of smoking, cutting down alcohol and intake of drugs), will be evenly provided to both the groups as part of routine care by the discharging nursing officer.

Two specially designed booklets will be provided to the patients to standardize the health education delivered to the patients verbally. The first booklet will contain information regarding the step-up plan of exercise following MI in both hospital and home settings. The second booklet gives information regarding lifestyle modifications following MI, such as cessation of smoking, regular sleeping, and resuming sexual activities. Both the booklets will be provided to the control and intervention groups. Furthermore, to enhance knowledge on different food choices under each category/color, a food poster will be given to the patients who will be following the plate model diet.

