### Measurement tools

#### Anthropometric measurements

Anthropometric measurements will be performed using calibrated equipment by a research assistant adhering to the WHO guidelines [29]. Height will be taken to the nearest 0.1 cm, as the maximum distance to the uppermost position on the head from the heels, with the individual standing barefoot and in full inspiration using a standard stadiometer (Seca 823; Seca, Hamburg, Germany). Body weight will be measured to the nearest 0.1 kg using an electronic weighing scale (Seca 803) with the participants wearing light indoor clothing. BMI will be calculated as weight in kilograms divided by height squared in meters (kg/m^2^). WC will be measured midway between the iliac crest and the lower rib margin at the end of normal expiration using a plastic, nonelastic flexible tape to the nearest 0.1 cm. Hip circumference will be measured at the widest level over the greater trochanters using a plastic flexible tape to the nearest 0.1 cm. Seated BP will be measured after at least a 10-minute rest using a mercury sphygmomanometer (model 0125; Accoson, Harlow, UK).

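### Seeing the two arms on different working days, with no rotation stated, gives the blinded clinic team a possible cue to allocation and aligns arm with visit day at follow-up

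*Protocol article*

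**What the plan says.** All of the following is in the protocol article.

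- **Who is blind.** The Blinding section states: "The patient management team, including the consultant cardiologist, medical officers, and nursing staff, will be blinded to the nature of the intervention" that the patient has been assigned. The research assistant is not in that list.
- **How the blind is protected.** At follow-up, "the participants will be advised not to convey information regarding the nature of the intervention they are undergoing" to other participants or to the attending clinician. The reason given is "to avoid cross-contamination or breach of the single-blind study design, respectively".
- **How visits are arranged.** The next sentence of the same section says that "the participants within the control and intervention groups will be followed on different working days to ensure the quality of the study". It does not say whether days are rotated between arms, whether a given weekday belongs to one arm throughout, or whether the clinic team knows the arrangement.
- **How outcomes are measured.** Under Anthropometric measurements, "Anthropometric measurements will be performed using calibrated equipment by a research assistant adhering to the WHO guidelines". One scale model and one sphygmomanometer model are named, with no distinction by arm.
- **When.** Table 3 places weight, blood pressure, fasting blood sugar and ALT at baseline, 1 month and 3 months, and lipids at baseline and 3 months only. Baseline is collected during the hospital admission.

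**The concern.** The section protects the clinicians' blind by asking each patient to stay silent, then adds an arrangement that can get round that silence. If every patient on a given day belongs to the same arm, the day itself carries allocation information. Without the split, one slip unmasks one patient. With it, one slip can unmask a whole clinic session. Because there are only two arms, it can also identify the other arm's day.

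This matters because the blinded team provides the medical management, which Table 2 describes as individual and according to standard guidelines. The Sample size section leaves blood pressure, lipids, fasting blood sugar and ALT out of the calculation because drug treatment and adherence to it can shift them. All four are follow-up measures, and the Outcomes section lists them as secondary outcomes. A team that can infer the arm could treat the arms differently, and these outcomes are the ones most exposed to that.

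The second issue is alignment. If one arm is always seen on different days from the other, any influence that persistently follows the day enters the comparison between arms, and the analysis has little or nothing with which to separate it.

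**Working it through.** The protocol gives no figure to reproduce on this point, so the check is mainly a comparison of sections. Two illustrative calculations follow.

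**1. Is visit day a possible marker of arm?** Yes, as written. The Blinding section separates the arms by working day and states no rotation. The marker becomes useful to the clinic team only if they know or work out the rule. The document does not say that they do, and describes nothing that would prevent it. Intervention patients carry cues: they receive a plate, a poster and a food diary, and the diary is used for monitoring at follow-up visits (Study materials).

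**2. Does the baseline remove a day effect?** No. Baseline is taken during the admission, before clinic days apply. A change from baseline therefore keeps any day effect present at follow-up.

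**3. Which outcomes are exposed?**
- Weight: taken by a research assistant, a role not listed as blinded. Under Day 2 until discharge, a research assistant also gives the nutrition advice. Visit day adds little to what this role may already know.
- Blood pressure, lipids, fasting blood sugar, ALT: exposed through treatment decisions by the team that is meant to be blind.

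**4. How easily could one disclosure occur?** Inputs: 120 recruited and 20% total loss (Sample size); roughly equal arms, because allocation alternates (Randomization). Evaluable per arm = 120 × 0.8 / 2 = 48. The disclosure probability p per patient is assumed, and patients are taken as independent. Chance of at least one disclosure = 1 − (1 − p)^48; expected number of patients who disclose = 48p.

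| Assumed p | At least one disclosure | Expected patients disclosing |
|---|---|---|
| 1% | 38% | 0.48 |
| 2% | 62% | 0.96 |
| 5% | 91% | 2.4 |

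Without the day split, the last column is roughly the number of intervention patients unmasked. With the split, and a team that knows the rule, a single disclosure can label all patients seen on that arm's days.

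**5. What would a persistent day-linked weighing error do?** The offset b and the SD are both assumed, because the protocol gives neither. With no true effect and 48 per arm, SE = SD × √(2/48), and the two-sided rejection rate at 0.05 is Φ(b/SE − 1.96) + Φ(−b/SE − 1.96). Example: b = 0.5 and SD = 3 (percentage points of body weight) give SE = 0.612 and b/SE = 0.816, so the rate is 12.9%.

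| Offset b | SD 3 | SD 5 | SD 17.5 |
|---|---|---|---|
| 0.5 points | 12.9% | 7.8% | 5.2% |
| 1.0 point | 37.2% | 16.5% | 5.9% |

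The SD of 17.5 is the value at which 48 per arm gives 80% power for the 10% difference in Sample size: 10 / [(1.96 + 0.84) × √(2/48)] ≈ 17.5. The spread shows how far the result depends on assumptions. The protocol documents no mechanism that would produce such an offset.

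**The case against.** The strongest reply has four parts.

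- **Disclosure is not certain.** The team must know or infer the rule, and patients are told not to disclose. This stands. The arrangement can reveal allocation; the document does not show that it does.
- **Measurement is standardised.** A reader might infer that arm is confounded with staff, scale, operator or assay run. The document does not support that. Anthropometric measurements gives the same calibrated equipment models and one procedure for everyone, and no section ties staff, devices or laboratory runs to clinic days. Such confounding would arise only if these in fact differ by day.
- **A permanent arm-to-weekday link is not stated.** The text says only that the days differ. With recruitment over 12 weeks and follow-up until 12 weeks after the last patient (Study period), each arm would be seen on many dates, and ordinary drift would tend to average out. This also stands. Only an error that recurs on one arm's days would bias the result. For that reason the rejection rates above should not be read as the trial's expected false-positive rate.
- **Separation has a purpose.** Limiting contact between arms is reasonable in a dietary behaviour trial. Scheduling purely by due date would give this up, and fixed time slots by arm would replace alignment with day by alignment with time of day.

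These replies narrow the point. They do not remove the tension between the declared blind and an unrotated, arm-specific visit day.

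**Conclusion.** The point holds in limited form. As written, visit day can disclose allocation to the clinic team for everyone seen that day, provided staff know or infer the rule, and arm is aligned with visit day at 4 and 12 weeks (lipids at 12 weeks only). The main risk is to the clinicians' blind, and through it to blood pressure, lipids, fasting blood sugar and ALT. The added risk to the weight comparison from assessor unblinding is small.

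The document does not allow the size to be determined. The disclosure figures rest on an assumed per-patient probability and independence, and the rejection rates rest on an assumed offset and SD. Both are illustrations. This is a weakness worth correcting because correction is cheap. It is not evidence that the primary comparison is invalid.

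**What to change.** Replace the sentence on working days with one that keeps the arms apart but rotates them. For example: the two arms attend separate clinic sessions; the arm assigned to each weekday and time slot alternates on a schedule prepared in advance and withheld from the patient management team, so that each weekday and slot serves both arms equally; the same scale and measurement procedure are used on all days.

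This keeps the protection against contact between participants and breaks the lasting link between arm and weekday. It does not remove the cue entirely, because a slip could still label the patients attending that one session, but it would no longer label that weekday for the rest of the trial.

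The cost is slightly more complex clinic scheduling and one changed sentence. Trial status is given as recruiting, so at the time of the article the change could still apply to the visits not yet held.

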### Intervention

#### Day 1

After the study protocol is explained by an investigator and after queries have been answered, written informed consent will be obtained from the individuals who satisfy the eligibility criteria. Once consent is obtained, the participants will be given an interviewer-administered questionnaire, which includes data on age, physical activity, area of residence, level of education, household income, coronary risk factors, diagnosis on admission, mode of management, and drugs given at the ward. Data on dietary habits will be assessed using a validated food frequency questionnaire (FFQ) [19] in an interviewer-administered format. Data on physical activity will be collected using the interviewer-administered International Physical Activity Questionnaire–Short Form (IPAQ-SF) [28]. Subjects in the “moderate”/“high” physical activity categories will be considered as being physically active.

Anthropometric measurements will be performed using calibrated equipment by a research assistant adhering to the WHO guidelines [29]. The exact methodology is described under the “Anthropometric measurements” subheading below.

#### Day 2 until discharge

Once the initial evaluation is over, fasting venous blood samples will be obtained by a trained nursing officer or medical graduate for glucose and lipid estimation from all participants in the ward setting. A blood sample will be taken after a 10-h fast. Plain tubes will be kept at room temperature for 30 minutes before separating serum. Once serum is separated, tubes will be separated into several aliquots for different investigations and stored at −20 °C by placing them in an icebox before transporting them to the laboratory.

During the hospital stay, the patients will be engaged in a rehabilitation program from day 2 onward, and it will be commenced in parallel with the study by a team trained by the study investigators. Patients will be provided with information about the disease, the basic anatomy of the heart, and a step-up exercise program that includes breathing and cardiovascular exercise, and further details will be provided to patients regarding general lifestyle modifications recommended in the post-MI period. The information is provided at a rate at which it can be absorbed by the patients, giving due regard to their psychological needs. Furthermore, aspects of healthy dietary habits will be addressed in detail to achieve the goals of the study. The checklist that will be used to evaluate the progression of the education sessions is given in Table 1.

**Table 1 Tab1:** Post-myocardial infarction patient education checklist

Description		Date	✓
1	Basic structure of the heart		
2	What does heart attack mean?		
3	Treatment at the CCU		
4	What to do in case of a chest pain (i.e., use of GTN)		
5	Gradually increasing level of physical activity		
6	Personal care		
7	Return to work		
8	Driving		
9	Traveling		
10	Sexual activity		
11	Ways to minimize psychological stress		
12	Cessation of smoking		
13	Use of alcohol		
14	Diet		
15	Stress		
16	Sleep and rest		
17	Discharge drugs		
18	Emergency contacts, clinic follow-up visits		

*CCU* Coronary care unit, *GTN* Glyceryl trinitrate

As part of this 12-week hospital- and home-based intervention, each participant in the intervention group will be provided with a model plate along with the food poster and a food diary. The patients will also be provided with nutrition advice that will be customized according to patients’ social, economic, and personal preferences by a trained research assistant (PF) with close supervision of a nutrition specialist (RJ). Advice in other domains, such as physical activity and lifestyle modification (e.g., cessation of smoking, cutting down alcohol and intake of drugs), will be evenly provided to both the groups as part of routine care by the discharging nursing officer.

Two specially designed booklets will be provided to the patients to standardize the health education delivered to the patients verbally. The first booklet will contain information regarding the step-up plan of exercise following MI in both hospital and home settings. The second booklet gives information regarding lifestyle modifications following MI, such as cessation of smoking, regular sleeping, and resuming sexual activities. Both the booklets will be provided to the control and intervention groups. Furthermore, to enhance knowledge on different food choices under each category/color, a food poster will be given to the patients who will be following the plate model diet.

#### Follow-up visits

The adherence to the intervention among the study participants will be scrutinized with the use of a self-maintained food diary. The compliance will be reinforced by regular follow-up calls by a research assistant (PF) and monitored at follow-up clinic visits using the FFQ at 4 weeks and 12 weeks following recruitment of the study subject.

As part of the research, data will be gathered for qualitative assessment of the knowledge, perception, and attitudes of the patients regarding the plate model diet during the follow-up visit at 4 weeks. This qualitative research is an integral part of the study that will provide insight into aspects such as adherence, feasibility, and practical problems encountered when the plate model is used in the Sri Lankan context.

### Study groups

The intervention arm subjects will be provided with the model plate, whereas subjects in the control arm will be provided with routine care, which is the only difference between the two groups. Otherwise, the management and clinic follow-up visits will be continued according to routine for all the patients recruited into the study.

### Study materials

“My rice plate” is a 3D plate made up of melamine, and the diameter is 10.5 inches. The title of the plate is printed in both local languages (Sinhala and Tamil) and English over the outermost border of the plate (Fig. 3). The plate is divided into five segments by printed lines. One-quarter of the plate is for rice, and another quarter is for protein-containing foods such as meat, chicken, fish, eggs, and soya products (textured vegetable protein). The remaining half is for nonstarchy vegetables. The segment representing the vegetables is again divided into three equal areas: one-third for green leafy salads (*mellum* in traditional Sri Lankan terms) and the other two-thirds for two different vegetables, including one green vegetable (Fig. 3). Each segment is colored with a color specific to that particular food group.

**Fig. 3 Fig3:**
[figure not shown]
A photograph of “My Plate” that is provided to the patients

The model plate will be supplemented with a food poster to educate patients on the food items in each group, which will also enhance compliance with the plate model diet. A food diary, which will be filled out by the patients while following the plate model diet, will be used to analyze compliance and will also be used as a monitoring tool during the follow-up visits. The model plate, food diary, and food poster will be the only intervention materials used in the study. A summary of interventions taking place for each group is provided in Table 2.

**Table 2 Tab2:** Comparison of interventions between the two arms

Arm A: test group	Arm B: control group
1. Provision of model plate “My rice plate” is a 3D plate made of melamine, which is designed to control portion size of each food group with visual reinforcement with different color segments assigned for each food group. Food poster will be provided to improve compliance with plate model diet, and food diary will be used as a monitoring tool in follow-up visits. 2. Each patient is given one-to-one education, with each session lasting about 5–10 minutes per day until the discharge, which comprises information regarding exercise as well as general lifestyle modification in post-MI period, such as cessation of smoking and cutting down alcohol. 3. Two separate booklets will be provided to the patients free of charge to reinforce the health education delivered to the patients verbally. 4. The rest of the medical management will be provided on an individual basis according to the standard guidelines and ward protocols.	1. Routine dietary advice will be provided, such as reduced intake of fat, sugar, and salt. Interventions 2, 3, and 4 in the control group will be the same as for the test group.

*MI* Myocardial infarction

### Study period

The recruitment period is estimated to span 12 weeks. The follow-up period is estimated to be 12 weeks from the day of the last patient recruitment. A further 2 months will be spent on data finalization, analysis, and report writing. Therefore, a total period of 8 months is estimated as the study period.

### Outcomes

The primary outcome is mean body weight reduction of 10% in the test group following the plate model diet for a period of 12 weeks compared with the control group. The following secondary outcomes will be evaluated in the test group compared with the control group at the end of the completion of the 12-week period from commencement of intervention: reduction of systolic and diastolic blood pressure, BMI, waist circumference (WC), hip circumference, waist-to-hip ratio, FBS, serum total and LDL cholesterol, serum ALT, and total caloric intake/day (FFQ), as well as improvement in level of physical activity (based on IPAQ-SF) and mean increment in serum HDL cholesterol level.

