### Sample size

The sample size will be selected on the basis of a pilot survey, and the number needed for recruitment will be determined to account for a confidence level of 95%, a confidence interval of 10%, and 80% statistical power. A 10% hypothesized difference of participants’ body weight between the control and intervention groups following the plate model diet at the end of 12 weeks is taken as the primary outcome when calculating the sample size. Because the other biochemical parameters (BP, lipid profile, fasting blood sugar [FBS], and ALT) are prone to vary with medication and compliance with medication, they were not regarded in sample size calculations. A subsequent 5% withdrawal rate and another 15% loss to follow-up (total of 20%) are accounted for in the calculation. A total sample of 120 will be recruited over an anticipated period of 3 months.

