### Study schedule

The detailed measurements that will be assessed at every visit are described in Table 3.

**Table 3 Tab3:** A brief study schedule at every visit

	On admission	Visit 1 (1 month)	Visit 2 (3 months)
Informed consent form	*		
Recording demographic data	*		
Medical history taking	*		
Physical examination^a^	*	*	*
Blood pressure	*	*	*
FBS	*	*	*
ALT	*	*	*
Lipid profile	*		*
Drug chart	*	*	*
FFQ	*	*	*
IPAQ-SF	*	*	*

*Abbreviations: ALT* Alanine aminotransferase, *FBS* Fasting blood sugar, *FFQ* Food frequency questionnaire, *IPAQ-SF* International Physical Activity Questionnaire–Short Form

^a^ Body weight, height, waist circumference, and hip circumference

* performing given activity/investigation in that perticular visits

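### Blood pressure, fasting glucose, lipids and ALT are worded as reductions from a loosely timed in-hospital baseline, which costs precision: adjust for that baseline and fix when it is taken

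*Protocol article*

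**What the plan says.** The Outcomes section of the protocol article sets a between-arm comparison at 12 weeks: "The following secondary outcomes will be evaluated in the test group compared with the control group". The quantities are worded as falls: "reduction of systolic and diastolic blood pressure, BMI, waist circumference (WC), hip circumference, waist-to-hip ratio, FBS, serum total and LDL cholesterol, serum ALT". HDL cholesterol is a mean increment. The section does not name the reference point for these falls. Table 3 ("A brief study schedule at every visit") has a single pre-intervention column, headed as the admission, so that is the only reference available.

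The timing of this baseline is described in three places:
- **Table 3** puts blood pressure, fasting glucose, ALT and the lipid profile at admission.
- **Day 1** (Intervention) covers consent, questionnaires and anthropometry.
- **Day 2 until discharge** covers the bloods (glucose and lipids are named): "Once the initial evaluation is over, fasting venous blood samples will be obtained by a trained nursing officer or medical graduate". The same section starts the rehabilitation programme on day 2 and includes detailed teaching on diet.

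Under Inclusion criteria, the index event may be up to one month old.

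On medication, the Sample size section says that blood pressure, lipids, glucose and ALT "are prone to vary with medication and compliance with medication, they were not regarded in sample size calculations". Table 2 says, for both arms: "The rest of the medical management will be provided on an individual basis according to the standard guidelines and ward protocols". In the Statistical analysis section, the methods named for continuous variables are the t test and analysis of variance, in a sentence about patient characteristics. No baseline-adjusted comparison is named.

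**The concern.** The stated aim is modification of cardiometabolic risk factors, and apart from weight these secondary outcomes carry it. They are left out of the sample size, so their precision depends on how efficiently they are measured and analysed.

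Two features work against that:
- **Form.** A reduction read literally is the 12-week value minus the baseline value. That subtracts the baseline at full weight, however weakly it predicts the 12-week value. A baseline taken during an acute admission, while treatment is individualised, may predict it weakly.
- **Timing.** Table 3 and the ward section do not give the same time for the bloods, and nothing requires the sample to precede the plate or the dietary teaching. Days since the event can also differ widely between patients. An analysis plan can add a covariate later, but it cannot change when blood was drawn.

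**Working it through.** **Is there a stated figure to reproduce?** No. The total of 120 rests on body weight, and the protocol gives no standard deviation, correlation or drug effect for these outcomes. The inputs below marked as assumed are therefore ranges.

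**Inputs.** Total 120 and 20% loss (Sample size): 120 × 0.8 / 2 = 48 evaluable per arm, taking equal arms. Two-sided 5% and 80% power. Assumed: 12-week SD = 1, baseline SD = k, correlation r.

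**Step 1: does a shared shift bias the comparison?** The effect detectable with 48 per arm is (1.960 + 0.842) × √(2/48) = 0.572 SD. A simulation used this as the true diet effect (a fall of 0.572), with r = 0.5 and 20,000 runs. A recovery or drug shift of 0, −1 or −3 SD was added to both arms:

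| Shared shift | Plate arm's own change | Between-arm difference | Power |
|---|---|---|---|
| 0 | −0.57 | −0.57 | 79% |
| −1 | −1.57 | −0.57 | 79% |
| −3 | −3.57 | −0.57 | 79% |

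The shift appears in full in the arm's own change and not at all in the comparison between arms.

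**Step 2: what does subtracting the baseline cost?** Per-patient variances:
- change score: 1 + k² − 2kr
- baseline-adjusted 12-week value: 1 − r²

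With k = 1 the ratio is (1 − r²) / [2(1 − r)] = (1 + r)/2. Power is for 48 per arm and an effect of 0.572 SD, by normal approximation (which gives 80% at r = 0.5, where the simulation gave 79%).

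| r (assumed) | Change variance | Adjusted variance | Ratio | Power, change | Power, adjusted |
|---|---|---|---|---|---|
| 0.2 | 1.60 | 0.96 | 60% | 60% | 82% |
| 0.3 | 1.40 | 0.91 | 65% | 66% | 84% |
| 0.5 | 1.00 | 0.75 | 75% | 80% | 90% |
| 0.8 | 0.40 | 0.36 | 90% | 99.3% | 99.7% |

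At r = 0.9 the ratio is (1 + 0.9)/2 = 95%.

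**Step 3: a more variable acute baseline.** With k = 1.5 the change-score variance is 1 + 2.25 − 3r:
- r = 0.2: 0.96/2.65 = 36%
- r = 0.3: 0.91/2.35 = 39%
- r = 0.5: 0.75/1.75 = 43%

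**Step 4: individual drug response.** In the simulation at r = 0.5, patient-to-patient variation in drug response of 0.5 or 1.0 SD lowers change-score power from about 79% to 70% or 50%. The between-arm difference stays at −0.57. Because this variation was added to the 12-week value independently of baseline, baseline adjustment does not remove it.

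**The case against.** The strongest reply is that the protocol already makes the right comparison. The Outcomes sentence sets the test group against the control group at 12 weeks, medical management follows the same rules in both arms, the treating team is blinded to allocation, and a drug chart is kept at every visit. That stands. A reader might infer that recovery and newly started drugs dominate the results and hide or distort the diet effect. The documents do not support this: no figure in them shows dominance, no within-arm test is planned, and Step 1 shows that a shared shift cancels. Bias would need drug treatment or recovery to differ by arm. Allocation by alternation weakens the assurance of balance, but that is a separate matter.

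Second, a change-score analysis is inferred. Lower values than control at week 12 is another possible reading, and regressing the change on arm and baseline gives the same arm estimate as regressing the 12-week value on arm and baseline. An analysis plan may already hold that model. This too stands in part: absence of a covariate from a protocol article is not itself an error. The form of the outcome and the timing of baseline are nevertheless protocol content, and on timing the article gives two accounts.

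Third, low correlations favour the point. With equal SDs the saving falls to 5–10% at r = 0.8–0.9. The Sample size section ties medication only to blood pressure, lipids, glucose and ALT, so the argument is weaker for BMI, waist and hip.

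Finally, the ward section mentions the blood draw before the rehabilitation programme. It gives no order within day 2, so sampling after teaching is possible but not established.

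**Conclusion.** The point holds as one of precision and baseline timing on secondary outcomes. It is not one of bias. For blood pressure, fasting glucose, lipids and ALT, simple change scores from the in-hospital baseline would be less efficient than a baseline-adjusted comparison. Adjusted variance is 60% of change-score variance at r = 0.2, 75% at r = 0.5 and 90% at r = 0.8 with equal SDs, and about 36–43% for r = 0.2–0.5 if the acute baseline has 1.5 times the 12-week SD. The correlations, the SD ratio and the 0.572 SD effect are assumptions, so the true gain could be substantial or small. The mismatch between Table 3 and the ward section on when bloods are taken can be read directly from the article and does not depend on those assumptions.

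**What to change.** 1. **Outcome definition.** For blood pressure, fasting glucose, lipids (including HDL) and ALT, state the estimand as the between-arm difference in the 12-week value, adjusted for the baseline value already collected (ANCOVA). The same form can be used for weight and the anthropometric outcomes, where the acute-phase argument is weaker.
2. **Baseline timing.** Reconcile Table 3 with the section on day 2 until discharge, so that all baseline measurements and bloods are taken at one defined point before the plate and dietary teaching are given.
3. **One recorded item.** Record days since the index event; eligibility already requires that event to be dated to within a month.

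The cost is a rewording of the outcomes and one scheduling constraint on the ward, with no added visits, samples or patients. The presentation becomes less simple than a reduction from baseline, although mean changes by arm can still be tabulated as description.
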